# The effect of lowering salt intake on ambulatory blood pressure to reduce cardiovascular risk in chronic kidney disease (LowSALT CKD study): protocol of a randomized trial

**DOI:** 10.1186/1471-2369-13-137

**Published:** 2012-10-19

**Keywords:** Dietary sodium, Chronic kidney disease, Blood pressure, Cardiovascular disease, Arterial stiffness, Clinical trial, Patient compliance, Taste disturbance

## Abstract

**Background:**

Despite evidence implicating dietary sodium in the pathogenesis of cardiovascular disease (CVD) in chronic kidney disease (CKD), quality intervention trials in CKD patients are lacking. This study aims to investigate the effect of reducing sodium intake on blood pressure, risk factors for progression of CKD and other cardiovascular risk factors in CKD.

**Methods/design:**

The LowSALT CKD study is a six week randomized-crossover trial assessing the effect of a moderate (180 mmol/day) compared with a low (60 mmol/day) sodium intake on cardiovascular risk factors and risk factors for kidney function decline in mild-moderate CKD (stage III-IV). The primary outcome of interest is 24-hour ambulatory blood pressure, with secondary outcomes including arterial stiffness (pulse wave velocity), proteinuria and fluid status. The randomized crossover trial (Phase 1) is supported by an ancillary trial (Phase 2) of longitudinal-observational design to assess the longer term effectiveness of sodium restriction. Phase 2 will continue measurement of outcomes as per Phase 1, with the addition of patient-centered outcomes, such as dietary adherence to sodium restriction (degree of adherence and barriers/enablers), quality of life and taste assessment.

**Discussion:**

The LowSALT CKD study is an investigator-initiated study specifically designed to assess the proof-of-concept and efficacy of sodium restriction in patients with established CKD. Phase 2 will assess the longer term effectiveness of sodium restriction in the same participants, enhancing the translation of Phase 1 results into practice. This trial will provide much-needed insight into sodium restriction as a treatment option to reduce risk of CVD and CKD progression in CKD patients.

**Trial registration:**

Universal Trial Number: U1111-1125-2149. Australian New Zealand Clinical Trials Registry Number: ACTRN12611001097932

## Background

Cardiovascular disease (CVD) is the leading cause of mortality in the chronic kidney disease (CKD) population, with CKD patients being 5–10 times more likely to die of CVD than to progress to end-stage kidney disease (ESKD) [1,2]. Dietary sodium intake has been associated with numerous modifiable risk factors for CVD in CKD including increased blood pressure (BP), volume overload, left ventricular hypertrophy, inflammation and endothelial damage [3-6] (Figure 1). Indicators of kidney damage, proteinuria and albuminuria have also been associated with sodium intake [6,7], and are key risk factors for subsequent all-cause and cardiovascular mortality [8,9]. However, despite evidence implicating dietary sodium in the pathogenesis of CVD in CKD, quality intervention trials in CKD patients are lacking.

**Figure 1 F1:**
[figure not shown]
**Simplified diagram of the relationship between excess sodium, kidney damage and risk of CVD.** Excess sodium in CKD is caused by decreased sodium excretion & high sodium intake (*influenced by food supply and preference – potentially mediated by taste sensitivity). This increases cardiovascular risk not only via altered extracellular volume & blood pressure (BP) but also through direct toxic effects on blood vessels.

Several meta-analyses of dietary sodium intake and blood pressure (BP) have been published, consistently demonstrating that a reduction in dietary sodium intake leads to reduced BP, particularly in hypertensive populations [10-14]. Unfortunately most studies included in these analyses exclude patients with kidney disease. Since sodium balance is primarily the role of the kidney, it is highly likely that CKD patients have a reduced ability to excrete the high sodium intake that is typical of a Western diet, increasing susceptibility to the adverse effects of excessive dietary sodium [15,16]. This may partially explain why hypertension is so prevalent in CKD, with data indicating that up to 70% of CKD patients are hypertensive [17].

An issue with translation of research in sodium restriction into practice is poor dietary adherence. This has been reported in several research trials [18-21]. Furthermore, data indicate approximately 80-90% of CKD patients consume more than 100 mmol of sodium per day [19-21], meaning that most do not adhere to the target set by evidence-based practice guidelines [22-26]. Achieving sodium restriction can be difficult in research and in practice. Therefore, it is vitally important to establish the feasibility of achieving adherence to sodium restriction in the clinical setting, as well as exploring the efficacy of this intervention.

Dietary sodium shows great promise as a modifiable risk factor for reduction of cardiovascular risk and risk of renal function decline in CKD, but high quality evidence is lacking. There is a need for a research trial showing the efficacy of sodium restriction for reducing the risks of CVD and CKD progression in CKD. Further, the effectiveness of recommendations to restrict sodium should be assessed to ensure the results are translatable to practice.

## Methods/design

### Study aim

The aim of the LowSALT CKD study is to examine the impact of reducing dietary sodium intake in decreasing cardiovascular risk in CKD patients. Our primary hypothesis is that a low sodium intake (LSI) (60 mmol/day) in patients with stage III or IV CKD will be independently associated with decreased ambulatory BP compared to a moderate sodium intake (MSI) (180 mmol/day). Our secondary hypothesis is that LSI (60 mmol/day) will result in the following outcomes compared with MSI (180 mmol/day): decreased arterial stiffness; decreased proteinuria and albuminuria; decreased extracellular fluid and markers of volume overload and thirst.

### Study design and setting

The LowSALT CKD study is a single-centre double-blind randomized cross-over trial (Phase 1) with a prospective observational follow-up (Phase 2). Phase 1 entails a 7-day run-in period followed by two, 2-week interventions (Figure 2). Participants follow a low sodium diet (goal: 60 mmol/day) together with either moderate sodium intake (achieved via slow-release sodium tablets providing 120 mmol sodium/day) or placebo (low sodium intake) for 2 weeks duration, and crossover to the other intervention with a 1-week washout in between (Figure 2). These levels of sodium intake represent two extremes of typical sodium intake in the Western diet, with the moderate sodium target (180 mmol sodium/day) representing that found in observational studies [19,27,28] and the low sodium target (60 mmol/day) resembling a level that meets even the strictest evidence-based practice guidelines specific to CKD [29]. Phase 2 involves a further 20-week observational period, where participants will be encouraged to adhere to a low sodium diet, and outcome measures repeated at 4 and 6 months (after commencement of Phase 1).

**Figure 2 F2:**
[figure not shown]
LowSALT CKD study flowchart.

### Ethical considerations

Ethical approval has been obtained through Metro South Human Research Ethics Committee and University of Queensland Human Research Ethics Committee.

### Target population and eligibility criteria

The target population for the trial will be stage III and IV non-dialyzed CKD patients. Eligibility criteria will include hypertensive, CKD stage III or IV (GFR 15–59 ml/min/1.73 m^2^) non-dialyzed, non-transplanted patients under the care of a nephrologist at the Princess Alexandra Hospital; aged ≥ 18 years with systolic BP 130–169 mmHg and diastolic BP ≥ 70 mmHg; non salt-wasting CKD (as diagnosed by nephrologist); prescribed ≤ 20 mmol sodium per day via medications; not pregnant or breastfeeding; life expectancy > 6 months; no current involvement in other intervention study and mental capacity to adhere to the study protocol (as indicated by medical team).

### Recruitment of participants

Potential participants will be identified through the outpatient clinic lists at the Princess Alexandra Hospital (PAH). To confirm that a potential participant’s blood pressure is within range, BP will be measured once in seated position when the participant attends clinic and previous BPs will be collected from the medical notes. Once a potential trial participant has been screened as meeting the eligibility criteria, recruitment by informed consent will be sought either at the time of the clinic visit or at a later date (providing additional time to consider the information). Once consented, patients will undergo 24-hour ambulatory blood pressure (ABP) measurement at baseline to confirm eligibility. Patients with 24-hour BP ≤ 130/70 will be discontinued from the study due to the potential risk of hypotension with sodium reduction. Patients and the treating doctors will be asked to keep the anti-hypertensive medications unchanged for the duration of the trial within bounds of patient safety.

### Dietary counseling

All patients will be counseled to follow a low sodium diet for the entire trial duration. Initial dietary education will occur face-to-face during run-in, with ongoing education during follow up visits and phone calls (Table 1). Topics covered will include: target sodium intake, general guidelines for following a low sodium diet, reading labels, foods and drinks high in sodium and lower sodium alternatives (individualized to participant’s usual dietary habits), low salt cooking methods and recipe ideas. In addition, participants will be provided with written dietary education materials (based on established resources used in CKD and heart failure patients to reduce sodium intake [30,31]). During Phase 1, participants will also be provided with a selection of low sodium foods to facilitate adherence to a low sodium diet (Table 1).

**Table 1 T1:** Strategies to facilitate sodium restriction

**Phase 1**	**- Dietary education (individualized) by accredited practicing dietitian**
	- Focus on replacing high sodium foods with low sodium alternatives (keeping energy intake stable).
	- Initial education in run-in with written materials provided
	- Ongoing education during follow up visits and weekly phone calls.
	**- Partial food provision**
	- Low sodium frozen pre-prepared meals (maximum 1 per day)
	- Snack foods, breakfast cereal, cheese and bread
**Phase 2**	**- Ongoing dietary education**
	- Monthly via phone calls
	- No food provided in this phase

### Randomization

An external statistical consultant will undertake the computer-generated randomization for the order of the intervention in blocks of 8, blinded to the investigators. To ensure all investigators and participants are blinded to the treatment, study medications are packaged off-site by an external pharmacy with a generic label as medication 1 and 2 for the first and second intervention.

### Intervention

As per Figure 2, following a 7 day run-in period, participants will enter ‘treatment’ (moderate sodium arm, 180 mmol/day) or ‘control’ (low sodium arm, 60 mmol/day) for 2 weeks duration and cross-over to the alternate treatment. During ‘treatment’ participants will receive 120 mmol sodium /day via slow-release sodium chloride tablets (4 × 10 mmol tablets t.d.s; Slow Sodium, Novartis Pharmaceuticals Australia Pty Ltd), in addition to 60 mmol dietary intake. During ‘control’, participants will receive white placebo capsules (4 × capsules t.d.s, size 1D cellulose capsules, Pharmaceutical Packaging Professionals Pty Ltd). A washout period (1 week duration) will precede intervention two; this period was chosen as previous research indicated this is the duration needed to achieve sodium balance [32]. During washout, participants will continue to consume a low sodium diet (goal 60 mmol/day).

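### Phase 1 is called double-blind, but the active product is tablets and the placebo is capsules, and a generic label alone does not make them indistinguishable

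*Protocol article*

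**What the plan says.** Under Study design and setting, the Protocol article calls Phase 1 a "single-centre double-blind randomized cross-over trial". Randomization gives the means of blinding: "To ensure all investigators and participants are blinded to the treatment, study medications are packaged off-site by an external pharmacy with a generic label", the labels being medication 1 and medication 2 for the first and second intervention.

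Intervention then specifies the two products. In the moderate-sodium period "participants will receive 120 mmol sodium /day via slow-release sodium chloride tablets", a named marketed product, taken as four 10 mmol tablets three times a day. In the low-sodium period "participants will receive white placebo capsules", described as size 1D cellulose capsules, four taken three times a day. Participants stay on each "for 2 weeks duration and cross-over to the alternate treatment", with a one-week washout between.

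The Discussion describes the comparison again as tablets against placebo and lists the blinding of participants and investigators among the features that reduce the risk of bias. The article does not mention over-encapsulation, a matching placebo tablet, a double dummy or any check of blinding.

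**The concern.** A label conceals identity only if the contents look alike. Here the stated dosage forms differ, and the crossover gives each participant both of them. In a parallel trial a participant would see one form and have nothing to compare it with.

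Blinding matters because Phase 1 is meant to hold diet constant and vary only the study product. Apart from partial food provision, participants choose their own food, with coaching at visits and in weekly calls. A participant who believes that a given period is the high-sodium one may relax or tighten the diet, and that changes the sodium contrast behind 24-hour systolic pressure. Outcomes that depend on report or on an operator can be affected more directly: the Xerostomia Index, the daily checklist and other diet records, and pulse wave velocity and pulse wave analysis by tonometry.

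**Working it through.** No figure in the plan measures blinding, so the check is mainly a comparison of its statements.

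1. **Claim.** Phase 1 is double-blind (Study design and setting); all investigators and participants are blinded (Randomization); blinding reduces bias (Discussion).
2. **Stated means.** Off-site packaging and a generic label (Randomization).
3. **Products.** Active: "via slow-release sodium chloride tablets". Placebo: white cellulose capsules (Intervention).
4. **Unit count.** Active: 4 tablets × 3 times a day = 12 a day, and 12 × 10 mmol = 120 mmol a day, which reproduces the stated supplement. Placebo: 4 capsules × 3 = 12 a day. Number and frequency are matched; form is not.
5. **Who meets both forms.** Every participant who completes both periods, because of the crossover.
6. **Who else may learn the form.** Staff hold visits and weekly calls (Dietary counseling, Table 1). The daily checklist, which includes a medication record, is verified, and pills are counted at trial end (Adherence/dietary intake measures). The article does not say who counts, or whether the checklist shows the form.

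Step 2 does nothing about the difference in step 3. Followed literally, the text yields two products that can be distinguished.

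**Route to the primary outcome.** Let *a* and *b* be the departures from the 60 mmol/day dietary goal in the moderate and low periods, with all study product taken. Then:

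contrast = (60 + *a* + 120) − (60 + *b*) = 120 + (*a* − *b*) mmol/day.

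If behaviour is the same in both periods, *a* = *b* and the planned contrast of 180 − 60 = 120 is kept. If participants act on a guess, *a* and *b* differ and the contrast shifts by the difference, in either direction. The article gives no basis for a value of *a* − *b*, so no effect in mmHg can be derived.

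**Safeguards in the article.** Ambulatory pressure is read by an automated device, and its results are masked to patients and investigators. Urine, bio-impedance and serum results are masked too. Urinary sodium (24-hour at follow-up points, mid-stream weekly in Phase 1) can show a change in diet. Tonometry has quality criteria: operator index above 80 for pulse wave analysis and standard error below 10% for velocity.

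**The case against.** The strongest reply is that a journal article condenses a full protocol, and that the pharmacy's preparation of the product is a detail often left out. The tablets may in fact have been put into matching capsules; the equal unit count and the stated purpose of the off-site packaging fit such an intent. This stands as a limit on certainty. It does not remove the point, because the article does not leave masking to another document: it states the measure and specifies both products, down to capsule size. If over-encapsulation was done, the description of the active product is wrong and needs correcting.

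A reader might infer more than the documents support, in four ways:

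- **That blinding has failed for participants.** Seeing that two products differ is not the same as knowing which contains sodium. The labels do not say, and the article does not show what participants are told about the form. A guess is a real risk, not a certainty.
- **That staff are unblinded.** This is an inference from possible participant reports, the checklist and the pill count. If trial end means after the second intervention, the count follows that participant's Phase 1 measurements and cannot bias them.
- **That fixed blocks of 8 let staff predict allocation, with selection bias.** Only the order is randomized and everyone receives both treatments, so predicting the order does not produce the selection bias it could in a parallel trial.
- **That the number of tablets and capsules taken measures the harm.** It measures exposure to a visible difference, not bias in the 5 mmHg contrast on which the trial is planned.

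The masked readings also count in the plan's favour. They protect against biased reading of results, but not against a change in what participants eat.

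**Conclusion.** The point holds as an inconsistency within the article: the double-blind claim does not follow from the products and the masking measure that it specifies. It reaches every participant who takes both products. Its effect on the estimates is unknown and cannot be calculated from the documents.

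The exposure is uneven. Dietary behaviour in each period, the self-reported xerostomia score, diet records and operator-dependent tonometry are most open to it. The primary outcome is partly protected, since detection bias is limited by masked automated readings; what remains is the dietary route, which urinary sodium can reveal but not prevent.

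The conclusion assumes that the Intervention section describes the products as participants receive them. If the active tablets are dispensed in capsules identical to the placebo, the concern about bias falls away and only an error of description is left.

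**What to change.** - **Preferred.** Have the external pharmacy make the two products indistinguishable, for example in the same opaque capsule, with a check that this does not alter the slow release. State it under Randomization and Intervention.
- **If already done.** Correct the product description under Intervention.
- **If it cannot be done.** Qualify double-blind under Study design and setting, Randomization and the Discussion, say who remains blinded and to what, and keep pill counting away from those who measure outcomes.
- **Optional.** Ask participants for a treatment guess at the end of each period, as a low-cost check.

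The first option costs a packaging instruction to a pharmacy already engaged, plus the release check. The second is wording only. The third is wording and a division of staff tasks. None changes the sample size or the planned analysis.

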### Primary outcome - ambulatory blood pressure

24-hour ABP was selected as the primary outcome as it is the most accurate reflection of BP, with measurements over an entire 24-hour period indicating diurnal variation, while avoiding error due to white-coat or masked hypertension [33-35]. Data will be measured at time points as per Figure 2 and will be analyzed as mean 24-hour BP, daytime BP and night BP.

ABP will be measured using the TM-2430 Ambulatory Blood Pressure Monitor (A&D Medical, Australia). This device is a non-invasive lightweight portable device that is validated in accordance with British Hypertension Society protocol, with A/A rating [36]. ABP measurements will be conducted according to the ‘Practice Guidelines of the European Society of Hypertension’ for clinic, ambulatory and self BP measurement [33] with systolic and diastolic BP recorded every 20 minutes during the day (6 AM to 10 PM) and 30 minutes at night (10 PM to 6 AM) [33,37,38]. The left arm will be used for measurement, except when medical history indicates an existing claudication. The measurement arm will be kept consistent during the study. ABP monitoring will be considered adequate if at least two-thirds of the measurements taken over the 24-hour period are satisfactory [33]. Participants will be trained on the use of the 24-hour BP monitor when they attend the clinic to have measurements taken, and will be asked to record their sleep and wake times during the BP monitoring period. Investigators and patients will be blinded to ABP results.

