### Statistical analysis

The primary outcome will be change in 24-hour SBP from matched pairs of study subjects (by cross-over design) from MSI to LSI. Prior data indicate that the mean response of matched pairs is a 5 mm Hg change in BP with a standard deviation of 7 mm Hg (unpublished data from Todd et al. [64]). If the true difference in the mean response of matched pairs is 5 mmHg, 23 subjects across both treatments (to give 46 data sets) will be required to give a power of 90% with error of 0.05. Accounting for an adjustment factor of 1.56 (drop out of 20%; drop-in of 0%), a total of 37 patients will be recruited and pass run-in.

Analyses will be undertaken by analysis of covariance (ANCOVA) adjusting for baseline values using STATA (Version 12 [65]). To test for time order effects, both the treatment and treatment order will be included in the model. If the treatment order is not found to be significant, treatment group will be left in the model. Probability values of <0.05 will be considered significant. Test for normality of the distribution of each variable will be performed separately for each treatment group.

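### The pooled two-thirds adequacy rule accepts a 24-hour blood pressure recording that has no night reading

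*Protocol article*

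**What the plan says.** All of the following is in the protocol article.

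- **Schedule** (Primary outcome - ambulatory blood pressure): readings are taken "every 20 minutes during the day (6 AM to 10 PM) and 30 minutes at night (10 PM to 6 AM").
- **Adequacy** (same section): "ABP monitoring will be considered adequate if at least two-thirds of the measurements taken over the 24-hour period are satisfactory". No minimum is given for the day or the night window.
- **Summaries** (same section): the data "will be analyzed as mean 24-hour BP, daytime BP and night BP". How the 24-hour mean is weighted is not stated.
- **Reason for the endpoint** (same section): among the reasons given is "measurements over an entire 24-hour period indicating diurnal variation".
- **Primary analysis** (Statistical analysis): "The primary outcome will be change in 24-hour SBP from matched pairs of study subjects". The size calculation assumes that "the mean response of matched pairs is a 5 mm Hg change in BP with a standard deviation of 7 mm Hg".
- **Eligibility** (Recruitment of participants): a baseline ambulatory recording is compared with 130/70, and patients at or below it leave the study.

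**The concern.** The rule pools two windows that are sampled at different rates. Day readings are three-quarters of the schedule, and the pass mark is two-thirds, so the day window can satisfy the rule alone. A monitor taken off at bedtime therefore produces an adequate recording. Such a recording cannot show diurnal variation and cannot enter the night analysis, although the endpoint was chosen partly for the first and the protocol plans the second.

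Three things are at stake:

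- **The paired difference.** If night readings are missing in one period of a pair and present in the other, the error does not cancel within the participant.
- **The night analysis.** It loses data from recordings that the protocol counts as complete enough.
- **The baseline check.** In a patient whose pressure falls at night, a day-only recording reads high against 130/70, so a patient whom the check is meant to remove could stay in.

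**Working it through.** **Inputs.** From the protocol article: the sampling intervals and windows, the two-thirds rule, a 5 mmHg effect, an SD of paired differences of 7 mmHg, 90% power and an error of 0.05. Assumed, not in the documents: a day-night systolic gap G of 10 to 15 mmHg, the same for everyone; a day-only rate p of 20%, independent between periods; and a two-sided test.

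**1. The plan's own figure.** A paired t-test (noncentral t) with effect 5 and SD 7 has power 0.891 with 22 participants and 0.905 with 23. The stated 23 is reproduced.

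**2. What the rule accepts.**
- Day: 16 h × 3 per hour = 48. Night: 8 h × 2 per hour = 16. Total 64.
- Pass mark: 64 × 2/3 = 42.7, so 43 readings.
- All day readings and no night reading: 48/64 = 75%, a pass.
- No night reading and 5 day readings lost as well: 43/64 = 67.2%, still a pass.
- Counting an extra reading at a window edge (49 + 16, 48 + 17 or 49 + 17) gives a day share of 73.8% to 75.4%. The result is the same.
- This takes the scheduled readings as the denominator. If only readings actually attempted count, a monitor switched off at bedtime scores 48 of 48.

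**3. Error in one recording.** Let D and N be the day and night means, with G = D − N.

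| Summary | Formula | Excess of a day-only recording | G = 10 | G = 15 |
|---|---|---|---|---|
| Plain mean of readings | 0.75 D + 0.25 N | G/4 | 2.5 | 3.75 |
| Time-weighted mean | (16 D + 8 N)/24 | G/3 | 3.3 | 5.0 |

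The relevant row is whichever mean the trial uses for its complete recordings.

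**4. Effect on precision.** If each recording is day-only with probability p, independently, and the error is s, the variance of the difference becomes 7² + 2p(1 − p)s². With p = 0.20, 2p(1 − p) = 0.32.
- s = 3.75: √(49 + 0.32 × 14.06) = 7.31; power with 23 participants 0.879.
- s = 5.0: √(49 + 0.32 × 25) = 7.55; power with 23 participants 0.859.

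**5. Effect on the mean.** If the day-only rate differs between treatments by d, the mean effect shifts by d × s. A shift of 1 mmHg needs d = 1/3.75, about 27 percentage points, with the plain mean, or 1/5 = 20 points with the time-weighted mean. With equal rates the gap itself cancels. What remains, for a time-weighted mean, is p × (day effect − night effect)/3. For a day effect of 4, a night effect of 7 and p = 0.20 this is 0.20 × (−3)/3 = −0.2 mmHg.

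**6. Weighting in complete recordings.** A plain mean gives night 16/64 = 25% against 8/24 = 33.3% of the clock. The level is then G/12 too high, 0.8 to 1.25 mmHg, but most of this cancels in the paired difference. The treatment effect changes by (night effect − day effect)/12 in size: with effects of 4 by day and 7 by night, 4.75 instead of 5.0.

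**The case against.** The best reply accepts the count and disputes the consequences.

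- **Weighting.** The article says only that a mean is taken. It does not commit to a plain mean, and the analysis plan, which is not shown, may settle this. That stands. A reader might infer that the trial under-weights night; the documents do not support that, and in complete recordings the offset would largely cancel anyway.
- **Size.** A reader might set the 5.0 mmHg error beside the 5 mmHg target and conclude that the rule could produce or hide the whole effect. That compares the error in one recording with a mean over the sample. It does not follow, and the upper figure also needs a time-weighted mean and a 15 mmHg gap.
- **Bias by treatment.** The article (Phase 2) says that sodium restriction may ease sleep apnea and edema, from which one might infer more night loss on the higher sodium intake. That sentence is a rationale for measuring quality of life. It says nothing about tolerance of the monitor, and treatment is double-blind. The mechanism is conceivable but has no evidence here.
- **Safeguards.** Measurement follows a cited hypertension guideline, which may set minima by window; that cannot be seen here, and the article states only the pooled rule. Participants are trained and record sleep and wake times, and an empty night window would be noticed when night pressure is analyzed. This makes the problem visible but does not change which recordings count as adequate for the primary outcome.

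**Conclusion.** The point holds for the adequacy rule. Followed as written, the rule accepts as a 24-hour recording one that contains no night reading, which defeats a stated reason for choosing the endpoint. This follows from the protocol's own schedule and needs no outside figure.

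The consequences depend on assumptions. A participant with a day-only recording in one period has a difference that is off by 2.5 to 5.0 mmHg if the day-night gap is 10 to 15 mmHg. At an illustrative 20% of recordings and a 15 mmHg gap, the cost is a few points of power, from 0.905 to between 0.88 and 0.86. Material bias in the mean effect would need night loss to differ clearly between treatments, which nothing in the documents shows. How often day-only recordings would occur is unknown.

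The weighting of the 24-hour mean is something to specify, not an error. The sample size reproduces and is unaffected. Severity: should be fixed.

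**What to change.** Apply the protocol's own two-thirds criterion to each fixed clock window: at least 32 of 48 scheduled day readings (48 × 2/3 = 32) and at least 11 of 16 scheduled night readings (16 × 2/3 = 10.7). State that scheduled readings are the denominator, and use the same rule for the baseline recording. Keep the clock windows for this rule; with windows set by each participant's sleep and wake times, the counts and lengths would vary from person to person.

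As a secondary clarification, define 24-hour SBP as (16 × day mean + 8 × night mean)/24, so that neither the unequal sampling nor uneven loss of readings changes the weight of night.

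The cost is a sentence or two in the protocol and a line of analysis code. Some recordings, probably few, will fail the stricter rule and will have to be repeated or treated as missing. Schedule, device and sample size stay as they are.
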